### Project phases

This is the second phase of a recently completed project (phase 1; figure 1), developed in line with the Medical Research Council framework for developing and evaluating complex interventions.^46^ Phase 1 of Co-STARS involved the co-production of the training package with young people from Black African and Black Caribbean backgrounds with lived experience of mental ill health. Interviews and focus groups with mental health professionals were also conducted to assess existing knowledge and identify areas where training interventions were necessary. Phase 1 of the Co-STARS programme (2023–2024) focused on the co-production of the training content and format through workshops and focus groups with Black young people, mental health professionals and community leaders. This formative phase identified key barriers to equitable care and generated the two training components evaluated in the current Phase 2 feasibility study (WP1 and WP2).

**Figure 1 F1:**
[figure not shown]
Phased approach to Co-STARS evaluation. This figure outlines the three planned phases: Phase 1 (co-production of MHL training), Phase 2 (feasibility evaluation) and Phase 3 (definitive multi-site trial). MHL, mental health literacy; RCT, randomised controlled trial; UKRI, UK Research and Innovation.

The following outputs from the first phase will now be evaluated in phase 2:

Lived experience-led training package delivered by young people within Black diaspora communities (evaluated as part of WP1).e-learning on culturally responsive care for mental health professionals (evaluated as part of WP2).

We will pilot the feasibility of the training outputs through a series of evaluations (figure 2), which will form the basis for our Phase 2 activities (figure 1). If we demonstrate acceptability and feasibility of the training package, we will seek funding to progress to Phase 3, which is a multi-site (across all four nations in the UK) large scale cluster randomised controlled trial (CRT).

**Figure 2 F2:**
[figure not shown]
Overview of work packages for Phase 2 feasibility evaluation development. This diagram summarises the four work packages and cross-cutting components, including public involvement, systems mapping and economic evaluation. UKRI, UK Research and Innovation.

## Methods and analysis

Trial status: Phase 2 trial recruitment started in March 2025 and is due to conclude in January 2026.

Phase 2 aims: We aim to undertake a pilot evaluation assessing the feasibility, acceptability and cost-effectiveness of a MHL package designed to promote equitable mental healthcare access and improve outcomes for underserved groups. We co-designed and co-developed the following work packages (WP; figure 2) based on close engagement with stakeholders and patient and public involvement and engagement (PPIE) :

WP1: Pilot CRT of lived experience-led MHL training in community settings.WP2: Pilot Stepped Wedge Cluster Randomised Trial (SWCRT) of e-learning for mental health professionals.WP3: Mixed-methods study: Systems mapping and systems change evaluation.WP4: Economic evaluation of WP1-3 to develop a framework to examine cost-effectiveness and social return on investment (SROI).

In addition to assessing impact, we will embed a mixed-methods realist-informed process evaluation to explore the mechanisms of change and resources required to support intervention reach and impact in the continued rollout. We will develop theories that explain how outcomes targeted by Co-STARS are achieved, for whom, why and under what circumstances (contexts). The process evaluation will comprise targeted searches for literature, using the principles of a realist synthesis, interviews with various groups of stakeholders and a document review. The process evaluation will be critical to understand how the implementation is achieved, how each of the interventions produces change and how context might affect implementation and outcomes, including impact on mental health inequalities. Although effectiveness will not be tested at this stage, a pilot randomised design is essential to evaluate feasibility of recruitment, randomisation, data collection and implementation procedures of this intervention. These feasibility outcomes will determine whether progression to a definitive multi-site effectiveness trial is justified and inform its design.

A completed SPIRIT 2025 checklist is provided as online supplemental material 1, detailing the corresponding page and line references within this protocol.

### Co-production and cultural considerations

Young people from Black African and Black Caribbean-diaspora backgrounds were actively involved throughout the co-production of this study. Discussions with participants highlighted that ‘Black’ is not a single ethnicity or culture, and experiences vary widely depending on the intersections of social identities. These reflections informed the development of culturally responsive training, emphasising the diversity within Black communities and the importance of recognising intersecting social identities. The co-production process ensured that the study design, measures and materials were sensitive to participants’ cultural and social contexts. The co-production extended beyond the study design to include co-development of the training content, delivery format and visual and verbal materials used within both the community and e-learning packages. Young co-researchers also contributed to piloting and refining outcome measures and feedback procedures.

#### WP1: pilot CRT of lived experience-led MHL training in community settings

Research question: Can a lived experience-led, community-delivered MHL training package be feasibly implemented and accepted within underserved Black communities?

Design: Pilot CRT assessing feasibility, acceptability and preliminary change in mental health knowledge, attitudes and help-seeking.

Objective: To assess the feasibility and acceptability of the MHL intervention delivered to underserved communities and assess the barriers and enablers to support the future implementation strategy/trial.

Design: An unblinded, pragmatic, feasibility CRT implemented within a specific underserved community in Birmingham. We will adhere to the CRT consort extension^47^ to ensure transparency and quality of reporting. A mixed methods realist approach will be adopted for the process evaluation.

Method: Recruitment of clusters and implementation of the intervention will occur over a 6-month time frame (months 4–9). Participants within the cluster will be consented and asked to complete pre-outcome/post-outcome measures. We will also conduct structured observations assessing the fidelity of intervention delivery, as well as two focus groups and semi-structured interviews with participants within the control and intervention arms, as well as young people delivering the training.

Data collection schedule: Baseline data will be collected immediately prior to training (T0), and follow-up data 3 weeks post-intervention (T1). Research assistants trained in Good Clinical Practice will oversee all data collection, supervised by the principal investigator.

Setting: We will target two constituencies in the West region of Birmingham and Black Country region. The West of Birmingham is a region with the highest proportion of Black African and Black Caribbean individuals in Birmingham (19% compared with 9% and 3.5% in Birmingham and UK, respectively), with over half of the population living in the top 10% decile for deprivation, meaning that these communities are likely exposed to a multitude of social risk factors for development of severe mental illness.^42^

Unit of randomisation: Middle layer super output areas (MSOAs) within Birmingham and the Black Country will serve as the units of randomisation (clusters) and will be randomly allocated on a 1:1 basis to receive the intervention or control. Each MSOA represents a geographically defined area with a population of approximately 5000–15 000 residents, providing an appropriate ecological unit for community engagement and potential linkage with routinely collected data in future phases.

Within each selected MSOA, the intervention will be implemented in community settings such as places of worship (eg, Black-majority churches), youth centres, community centres and youth residential settings that already serve local Black communities. To ensure feasibility and representativeness, we restricted the sampling frame for cluster randomisation to MSOAs with intermediate Black population density, based on the proportion of residents identifying as Black (African, Caribbean or Black British) in the 2021 Census. This restriction avoids areas where community engagement would be unfeasible (very low-density MSOAs) and reserves very high-density MSOAs for the future definitive trial. Importantly, if recruitment and delivery are feasible in intermediate-density MSOAs, it is likely to remain feasible in MSOAs with higher Black population density, providing a conservative test of feasibility.

Randomisation will use restricted (covariate-constrained) allocation to maintain approximate balance on (i) area-level deprivation and (ii) anticipated participant numbers (based on venue capacity and local population). The randomisation sequence will be generated by an independent researcher/statistician prior to implementation.

By design, concealing treatment allocation is not possible in this community-based feasibility study. Given the nature of the training intervention, blinding of participants and researchers is not feasible. However, the primary feasibility outcomes (recruitment and retention rates, measure completion and acceptability) are objective and unlikely to be influenced by allocation awareness.

Population: Participants aged 18–65 years, self-identifying as members or regular attendees of community settings within participating MSOAs, will be eligible. Inclusion criteria include age 18–65 years, residence within the selected MSOA and ability to provide informed consent. Exclusion criteria include inability to consent due to cognitive impairment or severe current psychiatric crisis. Researchers will recruit participants through community champions and youth networks, provide study information sheets and obtain written informed consent prior to baseline assessment.

Intervention: The intervention is the lived experience-led MHL training. The training will be delivered by young people of Black African and Black Caribbean diaspora, lasting approximately 1.5 hours and will cover: (1) symptoms and signs of mental illness (including SMI); (2) how to distinguish mental health symptoms from normal behaviours; (3) attitudes and beliefs about people with mental illness; (4) advice on how to manage well-being; and finally, (5) information about local services and help-seeking. The intervention will be reported using Template for Intervention Description and Replication (TIDER).^48^

Control: Written MHL material (information leaflets and posters) placed within the community setting. Prior to these materials being placed in the community setting, participants will be invited to complete baseline measures and then re-approached after 3 weeks to collect follow-up measures.

Outcome: Feasibility outcomes include proportion of consenting clusters, percentage of training uptake and completion of pre-outcome and post-outcome measures, as well as the acceptability of the intervention and assessment of the barriers and enablers. Our secondary outcome is the assessment of key training outcomes: (1) *Knowledge*—The Mental Health Knowledge Scale^49 50^; (2) *Illness attributions and stigma*—Reported and Intended Behaviour Scale: Intended Behaviour Subscale to assess intended and reported stigmatising behaviours and desire for social distance from someone with a mental illness^51^; Community Attitudes towards Mental Illness scale^52^; and (3) *Help-seeking attitudes and efficacy*—General Help-Seeking Questionnaire.^53 54^ All instruments used have demonstrated robust psychometric properties in previous MHL research, including good internal consistency (Cronbach’s α>0.70) and construct validity.^49^,^54^

Sample size: We will recruit 120 participants from the eight randomised clusters. Formal power calculations are not necessary as no hypothesis testing for trial effectiveness is being evaluated.^55^ A sample of 120 (with ~60 per arm) meets sample size recommendations for pilot and feasibility studies and is sufficient to provide precision of feasibility parameters and estimates of study summary measures for a definitive trial.^56^ 20 participants in total will be recruited for focus groups (three groups of five diverse participants) and five 1:1 interviews.

Analysis: Descriptive statistics will be used to assess training fidelity and feasibility outcomes. Other data will be analysed using thematic analysis to generate important themes and patterns.^57 58^ For the secondary outcomes, means, CIs, intra-cluster correlation coefficient (ICC) of the outcome measures (both within-study and between-study clusters) will be estimated to determine which outcome(s) are most sensitive to change and provide sample size calculation for definitive trial.

ICCs for each quantitative outcome will be estimated using mixed-effects regression models including a random intercept for clusters, following the approach recommended by Hemming *et al* for cluster and stepped-wedge feasibility studies.^59^ Analyses will be undertaken in Stata (V.18). The ICC estimates, along with observed variances and completion rates, will inform the design of the definitive trial by (i) identifying outcomes that are most sensitive to change and (ii) providing parameter estimates for sample size and power calculations.

Missing data will be assessed for extent and pattern. The proportion of missing values for each variable will be reported, and exploratory analyses will assess whether missingness appears random or systematic. As this is a feasibility study, no formal imputation will be undertaken for primary feasibility outcomes; however, simple sensitivity analyses using mean or regression-based imputation may be conducted to evaluate the potential impact of missing data on secondary outcomes.^55 56^ The findings will inform strategies for minimising and handling missing data in the future definitive trial.

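### WP1 wrongly rules out allocation concealment: the list for all eight MSOAs can be withheld until clusters and venues agree, and as written cluster consent and recruitment may depend on the arm

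*Protocol article*

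**What the plan says.** All places are in the protocol article.

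- **WP1, Method:** "Recruitment of clusters and implementation of the intervention will occur over a 6-month time frame", given as months 4–9.
- **WP1, Unit of randomisation:** MSOAs "will serve as the units of randomisation (clusters) and will be randomly allocated on a 1:1 basis to receive the intervention or control". Venues such as churches and youth centres lie inside the MSOAs.
- **WP1, Unit of randomisation, allocation method:** covariate-constrained, balancing area deprivation and "anticipated participant numbers (based on venue capacity and local population". On timing: "The randomisation sequence will be generated by an independent researcher/statistician prior to implementation".
- **WP1, Unit of randomisation, concealment:** "By design, concealing treatment allocation is not possible in this community-based feasibility study". The next sentence says that participants and researchers cannot be blinded. The paragraph then argues that the main feasibility outcomes, recruitment among them, are objective and so unlikely to be swayed by knowing the arm.
- **WP1, Outcome:** "Feasibility outcomes include proportion of consenting clusters".
- **Methods and analysis, Phase 2 aims:** "a pilot randomised design is essential to evaluate feasibility of recruitment, randomisation, data collection and implementation procedures of this intervention". These outcomes are to decide whether a definitive trial is justified.

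The article does not say whether clusters or venues agree before or after their arm is drawn or disclosed.

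**The concern.** Blinding concerns who knows the arm after assignment. Concealment concerns who knows it before the unit has committed to take part. A trial of face-to-face training against leaflets cannot be blinded, but that does not prevent concealment at cluster level. The protocol gives the first fact as though it settled the second, and so gives up a safeguard that it could have.

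The two arms ask different things of a venue: to host a session of about 1.5 hours, or to display leaflets and posters. If a venue knows which it is being asked for, its answer is about that request. Phase 3 is planned as a large cluster randomised trial and needs to know how many venues will accept either arm before the draw. Researchers who know an MSOA's arm can also choose which venue in it to approach.

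**Working it through.** **1. The plan's own figures.** 120 participants / 8 clusters = 15 per cluster, and 4 × 15 = 60 per arm. This reproduces the stated figure of about 60 per arm. No power calculation is given, and nothing below depends on one.

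**2. Is concealment possible under the stated method?** With eight clusters at 1:1 there are C(8,4) = 70 allocations. Covariate-constrained allocation keeps a balanced subset of these and draws one. It needs the covariate values of all eight clusters and fixes all eight arms at once. The list is produced by someone independent. Nothing in this procedure requires the result to be disclosed before clusters and venues agree, so the statement that concealment is impossible is wrong for the design described.

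**3. Which orders of events fit the text?**

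| Order | Shared window, months 4–9 | Sequence before implementation | Constrained draw |
|---|---|---|---|
| (a) Agree, draw, release, deliver | fits | fits | fits |
| (b) Draw on estimated numbers, arm open, approach venues, deliver | fits | fits | fits |
| (c) Assign each cluster as it joins | fits | doubtful | cannot be carried out as stated |

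The text allows both (a) and (b). Because it declares concealment impossible, nothing excludes (b). Under (b), replacing a venue that declines would also change the anticipated numbers on which the draw was balanced.

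**4. What would cluster consent measure under (b)?** Let pC be the probability that a venue accepts the control arm and pI the probability that it accepts the intervention arm. With equal numbers approached in each arm:

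- reported consent = (pC + pI) / 2
- willingness to accept either arm ≤ min(pC, pI)
- overstatement ≥ |pC − pI| / 2

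The document gives no acceptance rates. The values below are assumptions, shown only for the direction and form of the effect:

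| pC | pI | Reported | Either arm, at most | Overstatement, at least |
|---|---|---|---|---|
| 95% | 90% | 92.5% | 90% | 2.5 points |
| 95% | 80% | 87.5% | 80% | 7.5 points |
| 95% | 70% | 82.5% | 70% | 12.5 points |

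If pC = pI, this lower bound is zero.

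**5. Resolution.** With eight clusters, one cluster is 1/8 = 12.5 points. If 8 of 9 approached agreed, the exact 95% CI would run from roughly 52% to 100%. A pilot of this size could not detect or correct such an effect afterwards, so the protection has to come from the procedure.

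**6. After the fix.** With one simultaneous release after all eight have agreed, each arm is a 50% guess beforehand (4 of 8 right on average). With an open list all eight are known. The sample size does not change.

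**The case against.** The best defence is that the harmful order of events is inferred. Sharing months 4–9 does not mean that clusters are still being recruited once delivery has begun. Recruiting, drawing and then delivering within the window fits every sentence, and a sequence made before implementation need not precede cluster recruitment. The randomised unit is the MSOA, taken from a Census-based frame. Anticipated numbers can be estimated for candidate venues before any of them agrees, so the need for venue capacity does not settle the order. A condensed article may also leave the order to the full protocol. All of this stands, and for that reason the point is worded as what may happen.

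The concealment sentence is different. It is a positive statement, not an omission, and it is wrong whichever order was intended. The defence that the outcomes are objective does not help: a count can be objective while the decision being counted depends on the arm.

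Two further objections are fair. The acceptance rates are assumed, and the central example is smaller than one cluster. Recruitment was also due to end in January 2026, before the article appeared in March 2026, so the order of site set-up can probably no longer be changed. The first limits what can be said about size. The second moves the weight of the fix towards reporting.

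**Conclusion.** The point holds in a limited form. The protocol is wrong to say that allocation cannot be concealed, and it does not fix the order of agreement, draw and disclosure. If venues were approached with their MSOA's arm known, cluster consent and the recruitment rate may depend on the arm, and willingness to accept either arm goes unmeasured. The size of this effect cannot be derived from the document.

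Three stronger readings are tempting but unsupported:

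- **That clusters are recruited during delivery, or that venues do agree knowing their arm.** The text permits this but does not state it.
- **That feasibility of randomisation is not tested.** Generating the allocation, carrying it out and delivering each arm as allocated are all still observed. What may be missing is agreement given before the arm is known.
- **That arms are predictable to a stated degree.** Revealing clusters one at a time under unconstrained 1:1 would allow 4 + 128/70 − 0.5 = 5.33 correct guesses of 8 on average. The protocol describes no such sequential reveal, so this figure does not measure its plan.

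**What to change.** In the Unit of randomisation paragraph, replace the sentence on concealment with: blinding is not possible; allocation is concealed until cluster and venue agreement. In the same paragraph and under Method, state that:

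- venues in all eight MSOAs agree to accept either arm, with anticipated numbers fixed, before allocation is disclosed;
- the independent statistician makes one constrained draw for all eight and releases it only after the last agreement; delivery may still be staggered.

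Under Outcome, define cluster consent as the proportion of those approached that agree to be randomised.

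For any venue that agreed after disclosure, report the timing of its agreement relative to disclosure and consent by arm, and do not count it as consent to randomisation when planning Phase 3. This part remains usable if set-up is already complete.

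The cost is protocol wording and, where still possible, the order of site set-up. First delivery waits for the eighth agreement. No participants are added, and the independent statistician is already in the plan. One limit remains: participants who consent after release will still know their arm, so the recruitment rate should be reported by arm in any case.

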**Methods and analysis:**

We co-produced a culturally appropriate, place-based, tiered MHL training package (Co-STARS) to deliver within underserved Black communities and via an e-learning package implemented among staff within mental health trusts. The training will be evaluated in stages. First, a pilot cluster randomised controlled trial will assess the feasibility and acceptability (defined as participants’ perceptions of the training’s relevance, usefulness and delivery) of a lived experience-led MHL training package delivered by Black young people with experience of mental ill health, to underserved communities in Birmingham, UK. Acceptability will be quantified through participation and completion rates and explored qualitatively via focus groups and interviews. Second, a stepped-wedge cluster randomised trial will evaluate the feasibility of an e-learning training programme for mental health professionals. We will embed a process evaluation to explore change mechanisms and identify barriers and enablers for future implementation. Third, we will use realist-informed participatory systems mapping and novel epidemiological analyses to explore downstream effects (ie, improved care access for Black ethno-racial groups within the intervention areas). Last, a cost-effectiveness framework will be developed to assess whether the intervention is good value for money in future efficacy trials. In the cluster trial, eight clusters will be randomised to the intervention arm (face-to-face training in the community) and control arm (display of MHL materials) with pre- and post-assessments in 120 participants from 8 clusters, 3 weeks apart. In the stepped wedge trial, six clusters (clinical teams within NHS mental health trusts) including 120 NHS staff in total, will move from control phase to intervention phase in a stepped wedge manner, with pre-assessments and post-assessments.

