**Figure 3 F3:**
[figure not shown]
Co-STARS e-learning stepped-wedge rollout. This schematic shows the sequential rollout of the e-learning intervention across six clusters over the 12-month study period. *Forward Thinking Birmingham of Birmingham Women’s and Children’s NHS Foundation Trust (FTB of BWC NHS FT). **Early Intervention Services of Black Country Healthcare Foundation Trust (EIS of BCH NHS FT).

The training will be deployed in a staggered manner in line with the stepped wedge approach. Starting in the first Mental Health Trust (Forward Thinking Birmingham (FTB) of Birmingham Women’s and Children’s NHS Foundation Trust; please see setting for description) in month 4 and rolled out to the four teams in staggered intervals. The training will then be rolled out in the second Mental Health trust (Early Intervention Services (EIS) of Black Country Healthcare NHS Foundation Trust) with staggered implementation between months 6–9. Through the course of implementation, we will conduct staff focus groups and semi-structured interviews. Baseline (pre-training) and post-training (4 weeks later) data will be collected electronically via the NHS Learning Hub platform.

Setting: FTB, part of the Birmingham Women’s and Children’s NHS Foundation Trust, is a 0–25 years community and inpatient mental health service and is the primary mental health service regionally for this population. Within FTB, there are four specialised care pathways, including Youth Justice, Specialist Eating Disorders and Core mental health team and EIS, which offer intensive community support to young people with a FEP.

The second trust is Black Country Healthcare NHS Foundation Trust, in which we will target four EIS teams (Dudley, Walsall, Sandwell and Wolverhampton), which provides community support to young people with psychosis between the ages of 14 and 65 years.

Randomisation: Cross-over of clusters (clinical team; n=6) from control to intervention will occur approximately every 4 weeks.

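### The statement that 120 participants give sufficient precision counts heads and does not hold for the ICC, which 8 clusters (WP1) or 6 clusters (WP2) estimate very imprecisely

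*Protocol article*

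**What the plan says.** WP1, Sample size: "We will recruit 120 participants from the eight randomised clusters". It adds that "A sample of 120 (with ~60 per arm) meets sample size recommendations for pilot and feasibility studies" and that this number "is sufficient to provide precision of feasibility parameters and estimates of study summary measures for a definitive trial". WP2, Sample size, makes the same claim for 120 staff. Both sections dispense with a power calculation: "Formal power calculations are not necessary as no hypothesis testing for trial effectiveness is being evaluated".

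The units are clusters. In WP1, under Unit of randomisation, the clusters are middle layer super output areas (MSOAs), which "will be randomly allocated on a 1:1 basis to receive the intervention or control". In WP2 the Abstract gives "six clusters (clinical teams within NHS mental health trusts) including 120 NHS staff in total", and the Randomisation paragraph agrees: "Cross-over of clusters (clinical team; n=6) from control to intervention will occur approximately every 4 weeks".

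On use of the results, WP1, Analysis, says "The ICC estimates, along with observed variances and completion rates, will inform the design of the definitive trial", partly by supplying parameter values for sample size and power. WP2, Analysis, says that ICCs will be reported with 95% CIs for the same purpose. Neither section gives an assumed ICC, a design effect, an expected interval width or an argument from the number of clusters.

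**The concern.** Precision in a cluster design depends on how many clusters there are as well as how many people. For the ICC, the number of clusters dominates: between-cluster variance is estimated on 6 or 7 degrees of freedom in WP1 and 5 in WP2, however many people each cluster contains. A head count of 120 therefore cannot support a claim of sufficient precision for the ICC.

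This goes beyond detail left to an analysis plan. The protocol makes a positive claim of sufficiency, and the quantity for which the claim fails is one it intends to carry into the Phase 3 sample size. A Phase 3 cluster trial across four nations that relied on the pilot point estimate could be badly mis-sized. The missing power calculation is not at issue, since that is acceptable in a pilot.

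**Working it through.** **The plan's own figure.** No formula or inputs are given for 120, so there is nothing to reproduce beyond 8 × 15 = 120 and 6 × 20 = 120.

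**Inputs.** From the protocol: WP1 has k = 8 clusters allocated 1:1, hence mean size m = 15. WP2 has k = 6, hence m = 20. Assumed: equal cluster sizes, one measurement per person, and an estimated ICC of 0.05 (range 0.01 to 0.10).

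**Exact 95% CI for the ICC.** With r the estimated ICC, the one-way ANOVA ratio is F = (1 + (m − 1)r)/(1 − r). Each limit is (F/q − 1)/(F/q + m − 1), where q is the 97.5% (lower limit) or 2.5% (upper limit) point of the F distribution. Negative limits are set to 0.

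- WP1, arm fitted, df (6, 112): F = 1.70/0.95 = 1.789; q = 2.523 and 0.204. Lower limit −0.02, set to 0. Upper limit (8.78 − 1)/(8.78 + 14) = 0.34.
- WP1, arm not fitted, df (7, 112): 0 to 0.30.
- WP2, df (5, 114): F = 1.95/0.95 = 2.053; q = 2.680 and 0.165. Lower limit −0.01, set to 0. Upper limit (12.46 − 1)/(12.46 + 19) = 0.36.

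**Sensitivity to the assumed estimate.** Upper 95% limits:

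| Estimated ICC | WP1, arm fitted | WP1, arm not fitted | WP2 |
|---|---|---|---|
| 0.01 | 0.24 | 0.20 | 0.24 |
| 0.05 | 0.34 | 0.30 | 0.36 |
| 0.10 | 0.45 | 0.40 | 0.48 |

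At 0.10 the lower limits are only just above 0 (0.004, 0.007 and 0.010).

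**Consequence for Phase 3.** Design effect DE = 1 + (m − 1) × ICC. For WP1 at m = 15:

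- at the estimate: 1 + 14 × 0.05 = 1.7;
- at the limits: 1.0, and 1 + 14 × 0.342 = 5.8.

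A sample sized on 0.05 could be too small by 5.8/1.7 = 3.4-fold, or too large by 1.7/1.0 = 1.7-fold.

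**Chance of a zero estimate.** The ANOVA estimate is zero or below when F ≤ 1. With true ICC ρ, the probability is that of an F variate falling below (1 − ρ)/(1 + (m − 1)ρ).

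- ρ = 0.02: about 40% in WP1 and 38% in WP2.
- ρ = 0.05: about 24% in WP1 and 21% in WP2.

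**Feasibility rates.** For an 80% completion rate in WP1:

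- clustering ignored: 1.96 × √(0.16/120) = 0.072, or ±7 points;
- ICC 0.05, normal multiplier: 1.96 × √(0.16 × 1.7/120) = 0.093, or ±9 points;
- ICC 0.05, t on 7 df: 2.365 × √(0.16 × 1.7/120) = 0.113, or ±11 points.

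**The case against.** The strongest case against has four parts.

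- **The text says the ICC informs the design.** WP1 names it alongside variances and completion rates, WP2 already promises 95% CIs, and nothing excludes external ICCs. Phase 3 is not yet funded and will have its own protocol. This stands against a stronger reading that a reader might draw, that the pilot cannot size Phase 3 as planned: the documents do not say that a bare point estimate will be the sole input. It does not make the sufficiency sentence true.
- **The planned analysis respects clustering.** Both trials use mixed models with a random cluster intercept. That is so, and it confines the fault to the justification. A model that allows for clusters does not add clusters.
- **The interval rests on an assumed ICC and equal clusters.** That is true and must be stated with the figures. The conclusion survives the range from 0.01 to 0.10. A large-sample standard error gives a narrower 0 to 0.17 at 0.05, but it is unreliable with so few clusters, and 0.17 still means a design effect of 1 + 14 × 0.17 = 3.4.
- **Feasibility is the primary purpose, and rates lose only a few points.** This stands. The protocol article states no progression threshold that the wider intervals would breach.

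The claim also cites published guidance that is not available here. The conclusion rests on the protocol's own cluster counts and does not dispute that source.

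**Conclusion.** Wrong as written for the ICC; weakened but not overturned for feasibility rates. At an assumed estimate of 0.05 with equal clusters, the 95% CI is about 0 to 0.34 in WP1 (0 to 0.30 without arm) and 0 to 0.36 in WP2. Across estimates of 0.01 to 0.10 the upper limit lies between about 0.20 and 0.48.

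Two further inferences go beyond the figures. A zero estimate is a substantial possibility, but it is not likely, since its chance is below one half in each case worked. Nor is Phase 3 at risk of being several-fold wrong in both directions: in the WP1 example only understatement is that large.

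The conclusion is not fragile. With 20% loss (assumed, 12 per cluster) the WP1 interval at 0.05 widens to 0 to 0.37. The WP2 Setting paragraph lists four pathways in one trust and four teams in the other; if WP2 had 8 teams of 15, its interval would be 0 to 0.30. Repeated measurements on the same staff add no clusters.

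**What to change.** In both Sample size paragraphs, replace the sufficiency sentence with cluster-adjusted precision. For WP1, for example: 120 participants in 8 clusters estimate an 80% completion rate to within about ±11 percentage points (assumed ICC 0.05, t on 7 df); the ICC itself will be imprecise, and an estimate of 0.05 would have a 95% CI of about 0 to 0.34. WP2 needs the equivalent sentence for 6 clusters, with 0 to 0.36.

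In both Analysis paragraphs, state that the pilot ICC will be reported with its 95% CI. State also that Phase 3 will be sized over a range of ICCs that includes external estimates for comparable outcomes, with the pilot ICC as supporting evidence and not the sole input.

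The cost is a few sentences and a less favourable statement of precision. The design does not change and no extra participants are needed.
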